## Abstract

**Background::**

Diseases of the oral cavity (OC) with an infectious trigger such as caries and periodontal disease are extremely common in the general population and can also have effects at the cardiovascular level. The oral salivary flow, with its buffering capacity, is able to regulate the pH of the OC and, therefore, significantly contribute to the ecological balance of the microenvironment in which the oral microbiome (OM) develops. On the other side, when the quality/quantity of salivary flow is altered it is supposed the disruption of this balance with the potential increase in oral pathogens and triggered diseases. Among the endogenous substances able to exert a significant effect on the salivary flow and its characteristics, carnosine (Car), a dipeptide originally isolated in skeletal muscle, represents, thanks to the known buffering properties, a promising principle.

**Methods::**

We aimed this protocol to evaluate the quantitative/qualitative characteristics of the salivary flow in healthy volunteer subjects (n = 20) and in subjects suffering from common OC pathologies (n = 40), before and after 7 days of supplementation with SaliflussTM (Metis Healthcare srl, Milan, Italy), a Class I medical device on the market as 400 mg mucoadhesive oral tablets that has Car as the main ingredient.

**Discussion::**

Combining the characteristics of saliva with the OM and comparing them with OC pathologies, we expect to clarify their reciprocal relationship and, using quantitative proteomics techniques, to help clarify the mechanism of action of Car.

## Introduction

1

The pH of the oral cavity (OC) is a synthetic parameter that underlies a multifactorial process of continuous adjustment including the effect of saliva^[1]^ as a buffer and the contribution of the OC microbiome.^[2]^ In some diseases of the OC an impairment of these adjustment mechanisms is supposed to alter the normal flow of saliva and, consequently, the pH and the oral microbiome (OM)^[3]^ with the expansion of potentially pathogenic strains such as the most cited streptococcus viridans.^[4]^

Carnosine (Car) is an endogenous dipeptide, composed of β-alanine and l-histidine, that was originally discovered in larger amounts in skeletal muscle of some vertebrates, including humans, showing a greater dependence on non-oxidative forms of energy metabolism.^[5]^ This peculiar association with muscular tissue and its pH-buffering properties has led to associate Car with the intracellular acid-base homeostasis of muscles.^[6]^ More recently, the physiological role of Car has been expanded beyond the intracellular buffering properties, supporting a role in sarcoplasmic Ca^2+^ regulation and neutralization of reactive oxygen species (ROS). It is well known that ROS induce the formation of reactive electrophilic carbonyl species by reacting with lipids and sugars which, in turn, react with proteins forming irreversible adducts (AGEs, ALEs, and EAGLEs) and cross-links that may affect the cardiovascular wall matrix that becomes less distensible, especially during the aging process and/or diseases.^[7]^ Thus, it is thought that Car and, indeed, other histidine-containing peptides, may prevent chronic diseases via their anti-inflammatory, anti-oxidative, anti-glycating, anti-ischaemic, and chelating properties.^[8]^ Furthermore, the localization of Car in other tissues such as the brain, olfactory bulb, heart, stomach, pancreas, kidney has suggested further potential uses in preventing, for example, neurodegenerative disorder and cognitive function or the development of type II diabetes.

The OM is a relevant part of the whole human microbiome since it contains several different niches, with distinct microbial communities, colonizing the OC, including not only bacteria but also fungi, viruses, archaea, and protozoa. These communities form a complex ecological system that influences OC and systemic health. Indeed the prevalent oral diseases (OD), namely dental caries and periodontal diseases, are believed to be microbiota-related. Furthermore, several evidences support the theory that many systemic diseases are associated with an altered OM, among these the most frequently associated diseases are metabolic, such as diabetes, cardiovascular and oncological ones.^[9]^ For their prevalence worldwide, among OD, periodontal infections, including gingivitis and chronic periodontitis, are possibly the most prevalent human microbial diseases (HMD).^[10]^

To protect the OC from HMD, in the present project we chose Car as a possible preventive and/or therapeutic principle for its aforementioned multiple biological effects. Thus, we decided to test the safety and efficacy of Salifluss^TM^ (Metis Healthcare s.r.l., Milano, Italy) a 400 mg mucoadhesive oral tablet (13 × 4 mm), that recognize Car as the main ingredient, on healthy volunteer and in subjects affected by common OD.

## Aim of the study

2

The main objectives of this protocol are to estimate the quantity/quality of oral salivae and OM in healthy volunteers and in subjects affected by common OD, before and after 7 days of treatment with Salifluss^TM^, 1 tablet twice a day. The characteristics of oral saliva (Sal) that will be studied are (a) unstimulated and stimulated (paraffin-activated) salivary flow rates and pH and (b) quantitative proteomics (QP), on selected targets, representing the main proteins/components of OM.

By matching Sal characteristics with OM and comparing them with OD, we do expect to elucidate their mutual relationship; furthermore, using specific bioinformatics tools to analyze the data, before and after treatment with Car, we are looking to see its potentials on preventing/treating OD and, using QP, eventually elucidate the mechanism of action.

The study will take place at the Odontoiatric University Clinic (OUC), Istituto Stomatologico Italiano (ISI) of Milan, Italy, in a prospective, randomized, double-blind, and placebo-controlled fashion.

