### Subjects selection

3.1

Among subjects referring to the OUC, we will enroll, on a voluntary basis, n = 40 diseased subjects (Ds), aged 18–40 years having at least 1 of the following OD: (a) dental erosions, (b) caries, and (c) périodontopathies, for example, gingivitis or aggressive/chronic periodontitis.

The criteria for each OD were defined on the basis of commonly accepted grading scores in dentistry. Dental erosions will be counted; for caries, we will adopt the missing and filled dental criteria; for périodontopathies, we will record the probing depth, clinical attachment loss, plaque index, and bleeding on probing using a manual periodontal probe.

A complete medical and dental history will be obtained from all participants; all the volunteers must not present allergies/intolerances to the consumption of Car or take other food supplements or any type of drug treatment (interview). Exclusion criteria will be also smoking, pregnancy/lactation, and the presence of any systemic diseases such as cardiovascular and respiratory, diabetes mellitus, HIV infection, or inflammatory conditions causing non-plaque dependent OD. Patients eligible for the study will return to the OUC after being pre-screened. Before being enrolled in the study, participants will provide written and informed consent for use of their saliva samples and clinical data for scientific research purposes. The study is in accordance with the guidelines of the World Medical Association Declaration of Helsinki.

A control group (Cs) of 20 age-matched subject with periodontal health will be enrolled among the staff of the OUC. The number of subjects identified and considered sufficient for the research is based on a preliminary test conducted on the salivary flow obtained from the staff involved in the project. The schedule of enrolment, interventions, and assessments, and the flow-chart of the protocol are depicted in Figures 1 and 2.

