### Proteomics analysis

3.4

For proteomics analysis samples stored at −80°C will be thawed and kept on ice before sample preparation. Disulfide bonds of proteins will be reduced using dithiothreitol , and free thiol alkylated with iodoacetamide. Proteins will be digested using trypsin as digesting enzyme. To enhance protein purification, denaturation, and digestion, the above-mentioned passages will be done in S-trap column (PROTIFI, New York, USA). After digestion, peptides will be eluted from the S-trap column, and they will be derivatized with tandem mass tag reagents (TMT kit Thermo Fisher, Milan, Italy). Samples will be further purified, combined for multiplexing analysis, and concentrated. Liquid chromatography–high resolution mass spectrometry analysis will be performed at the Unitech OMICS of the University of Milan, using a Dionex UltiMate3000 nanoflow liquid chromatography (nanoLC) connected in-line with an Orbitrap Fusion mass spectrometer (Thermo Scientific, Milan, Italy).

Data analysis for protein identification and quantification will be carried out with Max Quant software and further filtered with Perseus (Max Plank Institute of Biochemistry, Germany). Networks and pathways analysis will be done with STRING (Swiss Institute of Bioinformatics) and Ingenuity Pathways Analysis (QIAGEN, Hilden, Germany) software.

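### The aim promises proteomics on selected targets, but none is listed, and the assay lets the reported proteins emerge from the data inside a primary outcome that covers any saliva parameter

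*Protocol article*

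**What the plan says.** Section 2 (Aim of the study) divides the saliva characteristics to be studied into two groups: (a) unstimulated and stimulated flow rates and pH, and (b) "quantitative proteomics (QP), on selected targets, representing the main proteins/components of OM". The article names no target protein and refers to no target list.

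Section 3.4 (Proteomics analysis) describes the assay. Samples are reduced, alkylated and digested with trypsin, and the peptides are labelled with TMT reagents. Then: "Samples will be further purified, combined for multiplexing analysis, and concentrated". The pooled material goes to nanoflow LC "connected in-line with an Orbitrap Fusion mass spectrometer". After that, "Data analysis for protein identification and quantification will be carried out with Max Quant software and further filtered with Perseus". "Networks and pathways analysis will be done with STRING" and with Ingenuity. The acquisition mode, the number of TMT channels and the allocation of samples to pooled sets are not given.

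Section 3.5 (Statistical analysis) defines the primary outcome as the treatment-related change in any of the saliva parameters under study and takes P < .05 as significant where appropriate. Samples that are missing for any cause are removed from the analysis.

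**The concern.** The aim speaks of targets that have been selected. The method contains no step that selects a target or ensures that one is measured. It identifies what it can, quantifies it, filters it and passes the result to network software. In such a workflow the list of reported proteins is an output of the data.

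This matters because of where the proteomics sits. Section 2 makes it a saliva characteristic, and section 3.5 makes any saliva parameter primary. A protein picked after filtering, when its change is already visible, would fit the wording of both sections and could be presented as a selected target and a primary result. Nothing in the text lets a reader tell a target chosen in advance from a protein chosen afterwards.

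A second, smaller issue is that TMT samples are measured in pooled sets. If several sets are needed, a protein quantified in one need not be quantified in another, and the plan gives no rule for that case.

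**Working it through.** The plan states no figure on this point, so there is none to reproduce. The check has three parts.

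**1. The sections side by side**

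| Section | What it fixes | What it leaves open |
|---|---|---|
| 2, Aim | Quantification of selected targets is a saliva characteristic | Which targets, and who selects them and when |
| 3.4, Proteomics | Whole-sample digest, TMT, pooling, identification and quantification, filtering, pathways | Acquisition mode; any step tied to targets |
| 3.5, Statistics | Change in any saliva parameter is primary; P < .05 | Which proteins count as parameters |

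Taken in order, the proteomics is a saliva characteristic, any saliva parameter is primary, and the proteins are whatever section 3.4 yields. The set of primary variables is therefore open until the data have been filtered.

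**2. Error rate**

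If m proteins are each tested at 0.05 and treatment has no effect, the expected number of false positives is 0.05 × m, whatever the correlation between proteins. One is expected for every 1 / 0.05 = 20 proteins tested. The document does not say how many proteins will be quantified, so m is left as a symbol.

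**3. Number of TMT sets**

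Inputs from the document:
- 40 diseased subjects, and "A control group (Cs) of 20 age-matched subject with periodontal health" (section 3.1), so 40 + 20 = 60 subjects.
- Two time points, baseline and day 7 (section 3.2).
- One or two saliva types go to proteomics; the article does not say which.

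Samples: 60 × 2 = 120 for one saliva type, and 60 × 2 × 2 = 240 for both.

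Sets = samples / (channels − reference channels), rounded up. Channels (6 to 18) and reference channels (0 or 1) are assumptions.

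| Channels | Reference channels | Sets, 120 samples | Sets, 240 samples |
|---|---|---|---|
| 18 | 0 | 7 | 14 |
| 16 | 0 | 8 | 15 |
| 10 | 0 | 12 | 24 |
| 6 | 0 | 20 | 40 |
| 6 | 1 | 24 | 48 |

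Across this range the samples cannot share one set.

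The chance that a protein is quantified in every set is (1 − q)^sets, where q is the chance of missing it in one set, taken as independent between sets. Both q and independence are assumptions.

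| q | 7 sets | 12 sets | 24 sets |
|---|---|---|---|
| 0.01 | 0.93 | 0.89 | 0.79 |
| 0.05 | 0.70 | 0.54 | 0.29 |
| 0.10 | 0.48 | 0.28 | 0.08 |

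The result runs from nearly complete to mostly incomplete, depending on a q that the document does not give. This measure also overstates the loss: at q = 0.05 an expected 95% of sets still carry the value.

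**The case against.** The strongest reply is that the two sections are compatible. Selected targets may mean that TMT data are acquired on everything and the analysis then concentrates on chosen main proteins. TMT is quantitative, the aim does not promise absolute concentrations, and relative values serve a before/after comparison if a subject's two samples share a set or a reference channel links the sets. A condensed article may also leave the target list, acquisition settings and set allocation to a full protocol.

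Much of this stands. A reader might infer that the plan commits to untargeted discovery and so cannot measure its targets. The document does not support that: it never states the acquisition mode, and the instrument does not settle it. A reader might also infer that certain named targets will be missing for whole groups of subjects, who would then be dropped under section 3.5. That fails too. No target is named, the aim speaks of main proteins rather than scarce ones, and the removal rule concerns missing samples, not a protein left unquantified in an available sample.

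The reply does not dispose of what the article itself fixes. Even on the compatible reading, choosing proteins after quantification and filtering is a data-driven choice, and section 3.5 lets it enter the primary outcome. The absence of a list alone would be a detail for another document. Its combination with a primary outcome covering any saliva parameter is stated here.

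**Conclusion.** The concern holds in this form: the aim refers to selected targets, none is listed, the described workflow lets the reported proteins emerge from the data, and the primary outcome is worded so that these proteins fall within it at P < .05. This rests on reading the saliva parameters of section 3.5 as the saliva characteristics of section 2, which is the natural reading but takes one step of inference.

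The consequence for error is one expected false positive per 20 proteins tested under no effect, with the number of proteins unknown. Several TMT sets are needed at any plausible channel number (7 to 24 for 120 samples, 14 to 48 for 240), so a protein may not be quantified in every subject. How often that happens cannot be derived from the document, and the completeness figures above are illustrations only.

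The point should be settled before the study starts. It is not evidence that the assay is unsuitable.

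**What to change.** Reconcile sections 2 and 3.4, and adjust section 3.5 to match.

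- **Preferred:** state in section 2 that the proteomics is an exploratory analysis of relative abundance. In section 3.5, limit the primary saliva parameters so that proteomics is outside them, and apply false-discovery-rate control over all quantified proteins, not only those chosen for reporting.
- **Alternative, if selected targets are kept:** fix and date the list before any proteomics data are seen, so that targets can be told apart from proteins found later.

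In either case, a sentence on how samples are allocated to TMT sets (for example, keeping a subject's two samples together) and on how a protein absent from some sets is handled would deal with the coverage question. Requiring a different acquisition method is not needed; that would be a method preference.

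The preferred change affects wording and analysis only, and the Discussion says the study has not started. Its cost is that the proteomics can no longer support a primary claim. That fits the mechanistic role the article gives it in the Abstract and Discussion.

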## Methods

3

### Subjects selection

3.1

Among subjects referring to the OUC, we will enroll, on a voluntary basis, n = 40 diseased subjects (Ds), aged 18–40 years having at least 1 of the following OD: (a) dental erosions, (b) caries, and (c) périodontopathies, for example, gingivitis or aggressive/chronic periodontitis.

The criteria for each OD were defined on the basis of commonly accepted grading scores in dentistry. Dental erosions will be counted; for caries, we will adopt the missing and filled dental criteria; for périodontopathies, we will record the probing depth, clinical attachment loss, plaque index, and bleeding on probing using a manual periodontal probe.

A complete medical and dental history will be obtained from all participants; all the volunteers must not present allergies/intolerances to the consumption of Car or take other food supplements or any type of drug treatment (interview). Exclusion criteria will be also smoking, pregnancy/lactation, and the presence of any systemic diseases such as cardiovascular and respiratory, diabetes mellitus, HIV infection, or inflammatory conditions causing non-plaque dependent OD. Patients eligible for the study will return to the OUC after being pre-screened. Before being enrolled in the study, participants will provide written and informed consent for use of their saliva samples and clinical data for scientific research purposes. The study is in accordance with the guidelines of the World Medical Association Declaration of Helsinki.

A control group (Cs) of 20 age-matched subject with periodontal health will be enrolled among the staff of the OUC. The number of subjects identified and considered sufficient for the research is based on a preliminary test conducted on the salivary flow obtained from the staff involved in the project. The schedule of enrolment, interventions, and assessments, and the flow-chart of the protocol are depicted in Figures 1 and 2.

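### Controls need only periodontal health, so a control with caries or erosions also meets the diseased definition, and the caries score as written leaves out current decay

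*Protocol article*

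**What the plan says.** Section 3.1 (Subjects selection) of the protocol article sets out the diseased group as "n = 40 diseased subjects (Ds), aged 18–40 years having at least 1 of the following OD", and then lists the conditions: "a) dental erosions, (b) caries, and (c) périodontopathies, for example, gingivitis or aggressive/chronic periodontitis". One condition is enough.

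The control group has one oral-health requirement: "A control group (Cs) of 20 age-matched subject with periodontal health will be enrolled among the staff of the OUC".

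The exclusions are given as "Exclusion criteria will be also smoking, pregnancy/lactation, and the presence of any systemic diseases such as cardiovascular and respiratory, diabetes mellitus, HIV infection", followed by inflammatory conditions that cause oral disease not due to plaque. Allergy or intolerance to carnosine, and use of supplements or drugs, are also ruled out. None of these removes a control who has caries or erosions.

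On measurement, the same section says "Dental erosions will be counted" and "for caries, we will adopt the missing and filled dental criteria".

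Section 2 (Aim of the study) describes the two populations differently. Saliva and oral microbiome are to be estimated "in healthy volunteers and in subjects affected by common OD", and the abstract likewise presents the 20 controls as healthy. Section 2 and the Discussion both expect to relate saliva and microbiome to oral disease.

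**The concern.** A comparison of healthy with diseased subjects needs definitions that cannot both apply to one person. Here the diseased definition has three branches and the control definition closes only one. A control with active caries would be analysed as healthy, while a clinic patient with the same finding would be analysed as diseased.

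The caries wording adds a second weakness. A score made of missing and filled teeth records past loss and past treatment; untreated decay adds nothing to it. Even if controls were screened for caries, this score alone could miss current disease.

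At stake are the Cs–Ds comparison of saliva and microbiome, and any statement that carnosine acts differently in healthy and diseased mouths. The second matters because section 3.5 frames the primary outcome in both Cs and Ds.

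**Working it through.** **Definitions side by side (section 3.1)**

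| Condition | Makes a subject Ds? | Ruled out in Cs? |
|---|---|---|
| Periodontal disease | Yes | Yes, by the periodontal-health requirement |
| Caries | Yes | No |
| Dental erosions | Yes | No |

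Two of the three conditions can be present in a control. The word healthy in the abstract and in section 2 is a description of the group, not an entry rule, so it does not close the gap.

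**The plan's own figure.** The article gives 20 Cs and 40 Ds (60 in all), resting on a preliminary test, with no effect size, standard deviation or power. There is nothing to reproduce, so what follows is an illustration only.

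**Inputs.** From section 3.1: 20 controls and 40 diseased. From section 3.5: type I error 5% (two-sided is assumed). Assumed, not in the documents: the share p of controls with caries or erosions; a true standardised difference d between disease-free controls and Ds; and affected controls having the same mean as Ds.

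**Formulas.**
- Expected number of affected controls: 20p.
- Expected difference: d(1 − p). The control mean is a mixture of (1 − p) healthy and p Ds-like subjects.
- Power (normal approximation): Φ( d(1 − p) / √(1/20 + 1/40) − 1.96 ), where √(1/20 + 1/40) = √0.075 = 0.274.
- Otherwise eligible staff to examine to find 20 unaffected: 20/(1 − p).

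**Example.** For d = 0.8 and p = 25%: 0.8 × 0.75 = 0.60; 0.60/0.274 = 2.19; 2.19 − 1.96 = 0.23; Φ(0.23) = 0.59.

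| p | Affected controls | Factor (1 − p) | Power, d = 0.6 | Power, d = 0.8 | Power, d = 1.0 | Staff to examine |
|---|---|---|---|---|---|---|
| 0 | 0 | 1.00 | 59.1% | 83.2% | 95.5% | 20 |
| 10% | 2 | 0.90 | 50.5% | 74.8% | 90.8% | 22.2 |
| 25% | 5 | 0.75 | 37.6% | 59.1% | 78.2% | 26.7 |
| 50% | 10 | 0.50 | 19.4% | 30.9% | 44.7% | 40 |

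At least one affected control is likely even when p is small: at p = 10% the chance is 1 − 0.9^20 = 88%.

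**What is not affected.** Section 3.3 assigns placebo to randomly selected subjects, 10 from Cs and 10 from Ds. Within either group, active and placebo subjects are drawn from the same population however it was labelled, so a mislabelled control does not bias that comparison.

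**The case against.** The other side has several good points.

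- **Overlap is allowed, not shown.** A reader might infer that the control group is contaminated. The article does not support that: it gives no dental findings for staff, and it takes a dental history from everyone, so some overlap would at least be recorded. Recording is not exclusion, however, and the gap in the rule remains.
- **The caries sentence describes scoring.** A reader might infer that one old filling makes a subject a case and that untreated decay never does. Entry is on caries; the missing-and-filled phrase comes in the next paragraph, on grading, and has no cut-off. It may also be a shortened name for the usual index that includes decay. What stands is that the text omits decay and needs correcting.
- **The factor (1 − p) rests on a doubtful equality.** Affected controls are periodontally healthy by definition, whereas Ds includes periodontal disease. Affected controls may therefore lie between the two groups, and the loss would then be smaller than tabulated.
- **The primary outcome is treatment-related change.** This is correct and limits the reach of the point, as shown in the working.
- **Staff as controls.** A reader might also infer that the controls are the people in the preliminary test, or that using staff breaks the blind. The article describes the two staff groups differently, does not say that they overlap, and gives no route to unblinding. Neither inference is part of this point.

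**Conclusion.** The point holds as a fault in the eligibility definitions. Cs and Ds are not mutually exclusive, the control rule does not deliver the healthy group that the abstract and aim describe, and the caries criterion as written leaves out current decay.

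The consequence is that the Cs–Ds comparison, and any reading of response by disease status, is open to dilution of unknown size. The documents give no prevalence, so no single figure can be defended. Under the assumptions above, 10% to 50% affected controls would remove 10% to 50% of the expected difference; with d = 0.8, power would go from 83% to between 75% and 31%. These are illustrations, and upper ones if affected controls resemble Ds only in part.

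The randomised active-versus-placebo comparison within Cs and within Ds stays unbiased. What suffers there is the meaning of a result in the stratum called healthy. This should be changed before enrolment, but it does not invalidate the trial.

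**What to change.** - Define Cs as free of all three listed conditions: no erosions, no caries and periodontal health. Establish this with the same dental examination and scoring as for Ds.
- Include the decayed component in the caries criterion, so that caries status reflects current disease. Keep missing and filled teeth as descriptive data.
- Make both changes together. Screening controls with a score that omits decay would leave part of the gap open.

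The cost is a change of eligibility wording, the same dental chart for controls, and more clinic staff to screen. About 20/(1 − p) otherwise eligible staff must be examined to find 20: 20/0.8 = 25 if p = 20%, and 20/0.5 = 40 if p = 50%. If p is high, the staff pool may be a real constraint. The Discussion says that the study has not started, so the change can be made before anyone is enrolled. Afterwards, affected controls could only be reclassified or dropped from a group of 20.

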### Administration of Car

3.3

Subjects understudy will be instructed to assume Salifluss^TM^ twice a day, in the morning and before bedtime. Salifluss^TM^ is a Class I medical device according to EU Dir. no 93/42/CE (as amended by EU Dir. No. 2007/47/CE), notified to Italian Ministry of Health with ID number 1810197/1810202. At recommended doses, the intake quantities of the substances meet the requirements and limitations set by the Italian Ministry of Health. As previously introduced, Salifluss^TM^ is a 400 mg mucoadhesive oral tablet (13 × 4 mm^2^) with smooth surfaces whose main ingredient is Car. The tablet should be placed in the gingival fornix and, thanks to its mucoadhesiveness, let to dissolve slowly. The dissolution time of the tablet is around 2 hours in normal salivation conditions. Placebo tablets, similar to Salifluss^TM^ ones, will be administered to randomly selected n = 20 subjects, 10/10 from Cs/Ds. An SMS reminder will be sent to all the subject reminding to take the pill.

Patients will be encouraged to report any adverse events and other unintended effects of trial interventions.

Attached the technical and safety data sheets, the certificate of analysis, and the sell-sheet of the extract of Cr.

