### Statistical analysis

3.5

Descriptive statistics of continuous variables understudy will be presented as mean ± SD; categorical variables were expressed as absolute numbers and percentages. The differences in continuous variables will be assessed using the Mann–Whitney *U* test when not normally distributed, and the Student *t* test when normally distributed. The *X*^2^ test was used to test for differences in categorical variables. The relationship between all variables before and after active/placebo treatment will be tested by Spearman correlation coefficients and their 95% confidence intervals.

The primary outcome variable is the treatment-related change in any of the Sal parameter understudy, before and after active/placebo treatment in Cs/Ds subjects by intention to treat criteria, that is, including all patients with adequate sampling before and after treatment (7 days). Differences in treatment-related changes between the groups will be analyzed in the context of covariance analyses (ANCOVA), which included terms for treatment and baseline values as covariates. Treatment effects were assessed by the least-squares mean change from the above ANCOVA model.

If relevant, the intra- and inter-observer variability of sampling, as well as measurements, a repetition of sampling and data analysis will be performed. For intra-observer variability the primary observer will sample/analyze the data on 2 different days; for inter-observer variability the sample/analysis will be performed, independently, by a second observer who was blinded to previous results. Intra- and inter-observer variability will be calculated as the coefficient of variance, which is the standard deviation of the difference between observations divided by their mean and multiplied by 100.

The size of the sample and the power will be calculated expecting a type I error rate of 5% or less. When appropriate, a value of *P* < .05 will be considered significant.

If samples are missing for any cause (eg, not compliance with the trial protocol, no follow-up, others) they will be removed from the analysis.

Data will be analyzed at the end of the study when all samples will be collected. Access to the data in anonymized mode will be provided to the investigators.

A computer statistical package will be used to validate the model and to perform the analysis (SPSS v.20, IBM, Armonk, New York, USA).

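### The implied 30:10 split among diseased subjects costs precision and, in a pooled ANCOVA without a group term, mixes treatment with disease; 20/20 avoids both with the same 60 subjects

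*Protocol article*

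**What the plan says.** Section 3.1 (Subjects selection) enrols "n = 40 diseased subjects (Ds), aged 18–40 years" and adds: "A control group (Cs) of 20 age-matched subject with periodontal health will be enrolled among the staff of the OUC". It describes the number of subjects as "considered sufficient for the research is based on a preliminary test conducted on the salivary flow obtained from the staff involved in the project". Section 3.3 (Administration of Car) sets the allocation: placebo tablets "will be administered to randomly selected n = 20 subjects, 10/10 from Cs/Ds". The active counts are not written out in the text, and the flow-chart is not shown here.

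Section 3.5 (Statistical analysis) defines the endpoint: "The primary outcome variable is the treatment-related change in any of the Sal parameter understudy", before and after active or placebo treatment in Cs/Ds subjects. It compares the changes by an ANCOVA whose only named terms are treatment and the baseline value. The same section says: "The size of the sample and the power will be calculated expecting a type I error rate of 5% or less". Section 4 (Discussion) states that the study has not begun.

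**The concern.** Three things stand out.

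- **Precision.** With equal variances, a two-arm contrast in a fixed number of subjects is most precise at 1:1. The controls have that ratio. The diseased, who make up two thirds of the trial, do not, and no reason is given.
- **Balance.** Because the ratio differs between the groups, the active and placebo arms differ in their share of diseased subjects. The named ANCOVA terms would not remove that difference if the two groups were analysed together.
- **Consistency.** One section treats the size as settled and sufficient. Another speaks of size and power as still to be calculated. A reader cannot tell which is meant.

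At stake are avoidable imprecision in the primary contrast and an overall estimate that could partly reflect disease status.

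**Working it through.** **Inputs from the protocol article:** Ds 40 and Cs 20 (3.1); placebo 10 in each (3.3); type I error 5% (3.5). By subtraction, active is 30 in Ds and 10 in Cs.

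**Assumptions, not in the document:** two-sided test, 80% power, equal variance in the two arms, no dropout. Effects are in units of the residual SD of the ANCOVA, because no SD or target effect is given. For that reason the total of 60 cannot be reproduced. The allocation can still be assessed without it.

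**1. Precision within each group.** SE = √(1/n₁ + 1/n₂).

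- Ds 30:10: √(1/30 + 1/10) = 0.365
- Ds 20:20: √(1/20 + 1/20) = 0.316, ratio 0.866, a fall of 13%
- Cs 10:10: √(1/10 + 1/10) = 0.447, unchanged by the fix

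Information is n₁n₂/(n₁+n₂): 30×10/40 = 7.5, against 20×20/40 = 10. Since 15×15/30 = 7.5, the 30:10 split does the work of 15:15, that is, of 30 subjects.

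**2. Detectable effect** (noncentral t, one degree of freedom removed for baseline; normal approximation in brackets).

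| Contrast | SE | Detectable at 80% | Power for 0.8 SD |
|---|---|---|---|
| Ds 30:10 | 0.365 | 1.05 (1.02) | 57% |
| Ds 20:20 | 0.316 | 0.91 (0.89) | 69% |
| Cs 10:10 | 0.447 | 1.33 (1.25) | 39% |

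**3. Overall contrast adjusted for disease group.** Combine the two groups by inverse variance.

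- Current: 1/(7.5 + 5) = 0.080, SE 0.283, detectable effect 2.80 × 0.283 = 0.79 SD
- With 20/20: 1/(10 + 5) = 0.0667, SE 0.258, detectable effect 2.80 × 0.258 = 0.72 SD

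The fall in SE is 9%. Pooled without a group term, 40 against 20 gives √(1/40 + 1/20) = 0.274, so moving to 30 against 30 (0.258) gains about 6%.

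**4. Mixing of treatment and disease.** Current share diseased: active 30/40 = 75%, placebo 10/20 = 50%. Suppose the change differs between Ds and Cs by δ for reasons other than treatment. A pooled comparison without a group term then carries a bias of (0.75 − 0.50) × δ = 0.25δ, less to the extent that the baseline value already separates the groups. With 20/20 the share is 20/30 = 67% in both arms and this term is zero.

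**5. What is lost.** The SE of the before-after change among diseased subjects on active, in units of the SD of that change, goes from 1/√30 = 0.183 to 1/√20 = 0.224, a rise of about 22%.

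**6. Sensitivity to equal variances.** With SDs s₁ (active) and s₂ (placebo), the two splits tie when s₁²/30 + s₂²/10 = s₁²/20 + s₂²/20, so s₁² = 3s₂². Allocation 20/20 is more precise unless the SD on active exceeds about 1.73 times that on placebo.

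**The case against.** The strongest case for leaving the split alone is that unequal allocation is a recognised trade-off. The stated aims include estimating saliva before and after treatment and using proteomics to study mechanism. Both draw on treated diseased subjects, so the 22% loss in step 5 is a real cost. The article is also a condensed text, and a reason for 3:1, or the results of the staff test, may be in a fuller document. Both points stand. The second is why neither the missing rationale nor the missing power figures are counted as errors. Against the first, the between-arm ANCOVA is the primary comparison, and 30:10 costs precision there.

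The imbalance matters only if the two groups are analysed together. The named terms allow that, but the article does not say so. If each group is fitted separately, only the loss of precision remains.

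Three stronger readings are tempting and not supported:

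- **That the trial can detect only effects above 1 SD.** This holds only for contrasts within Ds or within Cs. The overall contrast detects about 0.8 SD as designed. The unit is also the residual SD: in raw SD the 30:10 figure would be 0.91 or 0.75 if the baseline correlation were 0.5 or 0.7 (assumed values).
- **That power will be computed from the observed results.** The future tense in section 3.5 does not say this, the section mixes tenses throughout, and the study has not started.
- **That 60 is too few, or was set by feasibility.** No target effect is stated that the design could miss, and the basis actually given is the staff test.

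**Conclusion.** The point holds as an inexpensive improvement to the design; it does not show that the trial is undersized. Under equal variances, moving Ds from 30:10 to 20:20 cuts the SE of its active-placebo contrast by 13%, and the detectable effect falls from about 1.05 to 0.91 residual SD at the assumed 80% power and two-sided 5%. The gain overall is smaller, 9% with adjustment for group, and there is none in Cs. Equal ratios also remove by design the 75% against 50% imbalance in disease status. A group term in the ANCOVA would deal with that imbalance even at 30:10, but would not recover the lost precision. The 30:10 count rests on subtraction and should be checked against the flow-chart. The two statements on sample size conflict as worded, and that conflict needs only an editorial correction.

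**What to change.** 1. Randomise Ds 20 active to 20 placebo, with Cs kept at 10:10 and the total at 60. If 3:1 is preferred for the before-after or proteomic aims, keep it and state that reason.
2. Add disease group to the ANCOVA of the combined sample, whichever split is used.
3. Reconcile sections 3.1 and 3.5 so that one statement says whether the size is already set and on what basis, or is still to be calculated.

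Cost: a revised randomisation list, placebo tablets for ten more subjects, one model term and a few sentences, with no extra enrolment. The scientific cost is ten fewer diseased subjects on active, with the less precise before-after estimate shown in step 5 of the working. As the study has not begun, all of this can still be done.
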